### Outcome measures

2.8

#### Primary outcome

2.8.1

Pain intensity after treatment (10 sessions).

#### Secondary outcomes

2.8.2

Pain intensity during movement; neck disability; cervical range of motion; pressure pain threshold (PPT); temporal summation (TS); conditioned pain modulation (CPM); depression symptoms; pain catastrophizing; quality of life; analgesic intake; and global perceived effect. Secondary outcomes will be measured at baseline and posttreatment (10 sessions). Pain intensity and global perceived effect will also be measured in contact by telephone after 6 weeks randomization.

### Pain intensity—numeric rating scale

2.9

Pain intensity will be evaluated using a NRS, which is a simple and easy-to-use measuring scale that consists of a sequence of numbers from 0 to 10, in which 0 represents “no pain” and 10 represents “the worst pain imaginable.” Then, patients rate their pain based on these parameters.^[28]^ The pain evaluation will be carried out verbally with the patient reporting the pain intensity.

### Neck disability—neck disability index

2.10

Neck disability will be evaluated using the neck disability index (NDI) that consists of a 10-item questionnaire that assess the impact of pain on daily activities using a score from 0 to 5 for each section, with higher values indicating more severe impact. This instrument has been translated and cross-culturally adapted for the Brazilian population.^[29]^ It will be used to include patients with neck pain in the study.

### Cervical range of motion—fleximetry

2.11

Cervical range of motion will be measured with a fleximeter (Sanny, São Paulo, SP, Brazil). The intra-rater reliability of cervical range of motion was tested in 10 asymptomatic subjects by a single evaluator at 48-hour intervals. Reliability has already been estimated by calculating the intraclass correlation coefficients (ICC_2,3_) and it was reported as excellent for flexion (0.874; 95% CI: 0.473–0.969), extension (0.931; 95% CI: 0.716–0.983), inclination to the right (0.979; 95% CI: 0.919–0.995), inclination to the left (0.968; 95% CI: 0.873–0.992), rotation to the right (0.934; 95% CI: 0.746–0.984), and rotation to the left (0.832; 95% CI: 0.326–0.958).

To measure flexion and extension, the fleximeter will be positioned on the side of the head, over the ear, and the patients will be seated; for lateral inclination, the fleximeter will be positioned on the frontal region and the patients will be seated; for rotation, the fleximeter will be positioned at the central point of the head and the patients will be supine. Range of motion will be measured 3 times for each movement, and the mean value will be considered for statistical analysis.

### Pressure pain threshold—algometry

2.12

Pressure pain threshold (PPT) will be measured using a Somedic Type II pressure algometer (Somedic, Hörby, Sweden) consisting of a circular rubber probe (1 cm^2^). The intra-rater reliability of measurement of PPT was tested in 10 asymptomatic subjects by a single evaluator at 48-hour intervals. Reliability has already been estimated by calculating the intraclass correlation coefficients (ICC_2,3_) and it was reported as excellent for the posterior cervical region and shoulder girdle (0.972; 95% CI: 0.887–0.993) as well as for the tibialis anterior muscle (0.985; 95% CI: 0.945–0.996).

For PPT measurement, the circular algometer probe will be positioned perpendicular to the skin and applied at a uniform and constant rate of 40 kPa/s. The patients will be instructed to close their eyes and to press the algometer sensor when the pressure sensation becomes painful. Three measurements will be collected with 30 seconds intervals between them and the mean will be used for data analysis. Patients will be not allowed to see the algometer readings during measuring. Six PPT recording points on cervical and shoulder girdle areas will be evaluated bilaterally: 2 cm lateral to the C2,^[30]^ C5,^[31]^ T4, and T8 spinous processes, at the middle point of the upper trapezius muscle (between C7 and the acromion)^[32]^ and the levator scapulae (2 cm superior to the superior angle of the scapulae)^[33]^ and on the middle third of the right tibialis anterior muscle.^[34]^ All patients will have 3 demonstrations of the PPT measurement on their right superior limb to ensure that they understand the PPT concept prior to starting the measurements.

### Pain temporal summation

2.13

Temporal summation (TS) will be induced by a Somedic Type II pressure algometer (Somedic, Hörby, Sweden) with a circular rubber probe of 1 cm^2^. The intra-rater reliability of pain TS was tested in 10 asymptomatic subjects by a single evaluator at 48-hour intervals. Reliability has already been estimated by calculating the intraclass correlation coefficients (ICC_2,3_) and it was reported as good for upper trapezius muscle (0.710; 95% CI: 0.295–0.930). For TS, 10 stimuli will be performed with a pressure of 40 kPa/s up to the mean value obtained from algometry performed prior on the most painful upper trapezius or, if the pain is the same between the sides or there is not pain in the upper trapezius, the dominant upper trapezius. Each TS stimuli will be maintained for 1 second before being released and the stimuli will be spaced at 1 second intervals. A timer will be used to ensure that the intervals are respected and that the stimuli are maintained. Patients will be asked about their pain using NRS at the first, fifth, and tenth stimuli.^[35]^ To prevent sensitization interference from the previously performed pain pressure threshold evaluation, the test will begin 5 minutes after PPT evaluation.

### Conditioned pain modulation

2.14

Conditioned pain modulation (CPM) represents a pain modulatory phenomenon in humans such that pain perception may be decreased by a nociceptive stimulus applied distantly from excitatory site.^[36]^ A noxious stimulus will be used as a conditioning stimulus to induce a reduction in the perception of pain from another test stimulus.^[37]^ The conditioned stimulus for eliciting CPM will be the cold pressor test and the test stimulus will be the assessment of PPT on the upper trapezius muscle.

First, the patients will receive clear instruction about the test procedure. Next, for the conditioned stimulus, a hand on the side ipsilateral to the most painful neck pain region will be immersed in a water bath maintained at room temperature (22 °C) for 1 minute to standardize the hand temperature.^[37]^ In the case of bilateral pain, the patient will be instructed to report the more painful side. If there is no consensus on which side is the most painful, the dominant side will be used. Thereafter, patients will be instructed to immerse the same hand (up to the wrist) in an ice water bath maintained at 4 °C.^[38]^ Patients will be asked to keep their hand moving (opening and closing the hand to prevent warming around the hand)^[39]^ in the water bath for 1 minute. During the conditioned stimulus, after 30 seconds, patients will rate the perceived pain intensity of the ice water on an 11-point verbal numeric pain rating scale with responses ranging from 0 (“no pain”) to 10 (“worst imaginable pain”). After 1 minute of immersion, the patient will be asked to remove their hand of ice water bath.

The PPT measure (test stimulus) will occur at the middle point of the upper trapezius muscle (between C7 and the acromion) contralateral to the immersed hand before the conditioned stimulus and, in order to avoid distraction bias, immediately after removing the hand from the ice water.^[40]^ For analysis of CPM efficacy, the mean PPT measured before the cold pressor test will be subtracted from the mean PPT measured after the cold pressor test. Hence, a lower CPM value reflects less efficient endogenous pain inhibition.

### Depressive symptoms—the beck depression inventory

2.15

The depressive symptoms will be evaluated using the Portuguese version of the beck depression inventory (BDI). The scale consists of items including symptoms and attitudes whose intensity range from neutral to a maximum level of severity, rated from 0 to 3. It has 21 items related to sadness, pessimism, feeling of failure, lack of satisfaction, feeling guilty, self-deprecation, self-accusations, suicidal thoughts, crying crises, irritability, social retraction, indecision, distortion of body image, inhibition of work, sleep disturbance, fatigue, loss of appetite, weight loss, somatic concern, and decreased libido. Scores higher than 15 detect dysphoria and scores over 20 indicate depression.^[41]^

### Pain catastrophizing—pain catastrophizing scale

2.16

Pain catastrophizing will be performed with the Portuguese version of the pain catastrophizing scale (PCS) validated and adapted by Sehn et al.^[42]^ The PCS is a self-administered questionnaire that consists of 13 items to assess catastrophizers. The items are rated on a 5-point Likert-type scale in which both intensity and frequency information are represented, with the following 5 levels of response for each Likert item: (0) not at all, (1) to a slight degree, (2) to a moderate degree, (3) to a great degree, (4) and all the time. The total score is computed by summation of all items and the total score ranges from 0 to 52 points. Higher scores indicate greater catastrophizing of pain.^[42,43]^

### Quality of life—12-item short-form health survey—version 2

2.17

The quality of life assessment will be performed using the 12-Item Short-Form Health Survey (SF-12) version 2 questionnaire. This is a self-report measure that assesses physical (physical component summary—PCS) and mental (mental component summary—MCS) health on a scale of 0 to 100. Higher scores represent better levels of quality of life.^[44]^

### Analgesic intake

2.18

All patients will be asked to report all analgesic medications (both opioids and non-opioids) taken 1 week prior to evaluation. The name, means of delivery, dose, pills per day, and number of days used in the past week will be recorded. All opioid medications will be converted into an equianalgesic dosage of oral morphine.^[45,46]^ Non-opioid analgesic medications will be converted to acetaminophen equivalents using the conversion table.^[47]^ During the treatment, the patient will be asked to record any medication used for their neck pain. These records will be important to determine if there will be a change in a medication dose per week used during treatment in relation to medication dose used week prior to the treatment. In addition, it will allow the researchers to determine whether the results will be biased as a result of medication use.

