### Intervention

2.7

The patients will receive 10 consecutive days of treatment, with the exception of weekends. Each session will last around 1 hour, and it will be conducted by the same therapist during the same period of the day. After the initial evaluation, the patients will be randomly allocated to one of 4 groups: PBM + TENS group, PBM group, TENS group, and Placebo group. In the PBM + TENS group (n = 36) the patients will undergo the active PBMT and active TENS, in the PBM group (n = 36) the patients will be undergo the active PBMT and placebo TENS, in the TENS group (n = 36) the patients will undergo the placebo PBMT and active TENS, and in the Placebo group (n = 36) the patients will undergo the placebo PBMT and placebo TENS.

The equipment Antares (Indústria Brasileira de Equipamentos Médicos - IBRAMED, Amparo, São Paulo, Brazil) will be used for active and placebo photobiomodulation therapy (PBMT). Table 1 shows the parameters that will be used in the active PBMT.^[26]^ The patient will be prone. If laying prone is not possible, they will be seated. The treatment area will be defined as the painful area. A simulation of laser application will be performed for the placebo PBMT. The cluster probe will be positioned on the painful area for the same duration as active PBMT, the equipment will be turned on and set, but the trigger will be not activated, and no beam will be applied.

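### The planned comparison of medication dose during and before treatment sets neck-pain medication against analgesics taken for any reason, and the check for medication bias has the same gap.

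*Protocol article*

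**What the plan says.** Section 2.18 (Analgesic intake) describes two records.

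- **One-week report at an evaluation:** "All patients will be asked to report all analgesic medications (both opioids and non-opioids) taken 1 week prior to evaluation". Nothing restricts this by the reason for taking the drug. The details listed for collection are the drug, its route, its dose, the daily pill count and the number of days of use; the reason is not among them.
- **Record kept during treatment:** "During the treatment, the patient will be asked to record any medication used for their neck pain". This one is restricted by reason.

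The section gives the during-treatment records two uses. The first is to establish whether there is "a change in a medication dose per week used during treatment in relation to medication dose used week prior to the treatment". The second is that "it will allow the researchers to determine whether the results will be biased as a result of medication use".

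Opioids are put on an oral morphine scale. For the rest, "Non-opioid analgesic medications will be converted to acetaminophen equivalents using the conversion table".

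Section 2.8.2 (Secondary outcomes) lists analgesic intake and gives the timing: "Secondary outcomes will be measured at baseline and posttreatment (10 sessions"). Section 2.6 (Procedures) places evaluations before treatment and after the 10 sessions, with a telephone follow-up at 6 weeks.

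**The concern.** A change in dose is interpretable only if the same thing is counted at both times. Here the earlier quantity covers all analgesics and the later one only those the patient attributes to the neck. A patient who takes the same tablets throughout, some for headache or back pain, would show a lower dose during treatment than before it.

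Two uses of the data are at stake. A reported within-arm fall in weekly dose could come partly or wholly from the change of scope, and it would point towards the reduced painkiller use that the Introduction names as a possible benefit. The bias check would also be incomplete: an analgesic taken for another pain can still lower a neck pain score, yet the during-treatment record would not contain it. Doses never written down cannot be recovered at the analysis stage.

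**Working it through.** The protocol gives no figure for analgesic intake, so there is none to reproduce. The check is algebra on the two definitions.

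**Inputs**

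- Pre-treatment dose: all analgesics, one week (section 2.18).
- During-treatment dose: neck-pain medication only, expressed per week (section 2.18).
- s, the share of the baseline analgesic dose taken for reasons other than neck pain. The protocol does not give it. Assumed range: 0 to 50%.
- r, the true ratio of weekly neck-pain dose during treatment to that before. r = 1 means no change; r = 0.8 is an illustrative 20% fall.
- Use for other reasons is assumed constant.

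Opioids and non-opioids sit on separate scales, so the formulas apply to each scale on its own.

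**Step 1: change within an arm.** Set the baseline total to 1, made up of (1 − s) for neck pain and s for other reasons.

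- Change as the text defines it: (1 − s)r − 1
- True change in all analgesics: (1 − s)r + s − 1
- Difference, text minus truth: −s, whatever the value of r

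| s | Text, r = 1 | True, r = 1 | Text, r = 0.8 | True, r = 0.8 |
|---|---|---|---|---|
| 0% | 0% | 0% | −20% | −20% |
| 10% | −10% | 0% | −28% | −18% |
| 20% | −20% | 0% | −36% | −16% |
| 30% | −30% | 0% | −44% | −14% |
| 50% | −50% | 0% | −60% | −10% |

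Example at s = 30%, r = 0.8: the text gives 0.7 × 0.8 − 1 = −0.44; the truth is 0.56 + 0.30 − 1 = −0.14.

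**Step 2: difference between arms.** In absolute dose, the text omits the non-neck dose taken during treatment from each arm's change. If that dose has the same mean in every arm, it cancels in the between-arm difference. Randomisation makes baseline non-neck use equal in expectation. Equality during treatment also needs treatment not to alter that use, or the patient's labelling of a dose as being for the neck.

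**Step 3: the bias check.** The share of analgesic dose missing from the during-treatment record is s / [(1 − s)r + s]. With r = 1 this is s. With s = 30% and r = 0.8 it is 0.30 / 0.86 = 35%. The check cannot see this part in any arm.

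**Step 4: the posttreatment report.** Section 2.18 ties the one-week report to an evaluation, not to baseline alone, and sections 2.6 and 2.8.2 put an evaluation after the 10 sessions. Repeating the report there gives all analgesics over one week at both times, and the term −s disappears. That is a different comparison from the during-versus-before one in section 2.18.

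**The case against.** The strongest reply is that the listed secondary outcome is the one-week report at baseline and posttreatment, with the same scope, recall period and conversion each time, and that the during-treatment record is supplementary. A reader might infer that the secondary outcome itself carries a built-in fall. The protocol does not support that: read together, sections 2.6, 2.8.2 and 2.18 point to a matched pair of reports. This part of the reply stands.

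A second reply is that the trial is randomised and placebo-controlled, with patient and evaluator blinded (section 2.20), so an artefact common to all arms does not bias the comparison between them. A reader might infer a biased treatment contrast. For the absolute dose change that does not follow, as step 2 shows, and the protocol nowhere commits to an uncontrolled within-arm claim. This stands too. Labelling could still shift as pain eases, but nothing in the protocol shows that it would differ by arm.

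Third, the size is unknown. With no use for other reasons the artefact is zero, and the exclusions in section 2.5 (rheumatic, metabolic, neurological and cardiopulmonary disease) narrow such use. They do not remove it: common headache, low back or menstrual pain is not listed there. The contrast between recall and a running record might also matter, but the protocol does not show in which direction, so no part of the fall is attributed to it here.

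Fourth, a fuller form may record the reason for each drug. That is possible, but the article itself states both scopes and the sentence that joins them, so this is more than an omitted detail. The wording that the during-treatment record takes any medication does not close the gap either: it is still limited to the neck, and the stated conversions cover analgesics only.

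**Conclusion.** The point holds for two stated uses of the data. The during-versus-before change in weekly dose compares a subset with a total and understates the during-treatment dose by s of baseline: 0 to 50% over the assumed range, and nil if s is 0. The check on whether medication use biased the results misses analgesics taken for other reasons; randomisation does not make that check complete.

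The point does not extend to the between-arm difference in absolute dose change, which is unbiased in expectation if non-neck use and its labelling during treatment do not depend on the arm. Nor does it extend to the baseline-versus-posttreatment one-week report, whose scope appears to match. The conclusion rests on reading section 2.18 as written and on non-neck use staying constant. The correction is worth making before data collection, because unrecorded doses cannot be recovered.

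**What to change.** - **During treatment:** have patients record all analgesics, with a tick-box showing whether each was taken for neck pain.
- **At the baseline interview:** ask the reason for each drug as well, so that change can be computed in one scope, either all analgesics or the neck-pain subset, at both times.
- **Secondary outcome:** state that analgesic intake is the one-week all-analgesic report at baseline and posttreatment, compared between arms.
- **Bias check:** base it on all analgesics recorded during treatment.

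If enrolment has already begun, the minimum is to rest the change in intake on the two matched one-week reports and to present the neck-pain record as descriptive only.

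The cost is a small change to the patient record and interview form and slightly more recording by patients. Treatment and sample size are unaffected.

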### Global perceived effect—global perceived effect scale

2.19

The global perceived effect (GPE) scale, translated and validated for Portuguese, evaluates the patient's global perception of recovery. It consists of an 11-point scale that ranges from –5 (vastly worse) through 0 (no change) to 5 (completely recovered). At baseline, after the treatment, and at follow-up, the patients will be asked “Compared to when this episode first started, how would you describe your back these days?” A higher score represents a better condition.^[48]^

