## Introduction

1

Chronic neck pain is defined as pain or discomfort in the posterior cervical region between the superior nuchal line and the first thoracic spinous process and/or shoulder girdle with or without pain referred to the upper back or arms and continuing for at least 3 months.^[1–3]^ Neck pain is considered non-specific when it is not related to any specific pathology such as inflammatory rheumatic disease, osteoporosis, cancer, or radiculopathy.^[2]^

Neck pain has an incidence of 10.4% to 21.3% and a prevalence of 17.1% to 73%^[1]^ and it is increasing with population aging.^[4,5]^ It is estimated that 71% of the population will experience neck pain some time in their lives with women being more likely than men to experience it.^[1,4]^ According to Global Burden of Disease, in 2015, more than a third of a billion people had neck pain of >3 months duration and neck pain was ranked the fourth leading cause of disability-adjusted life years (DALYs) globally just after ischemic heart disease, cerebrovascular disease, and lower respiratory infection.^[5,6]^ With such a large population affected by this problem, increasing knowledge about effective treatments for it should be considered a global health priority.

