Both therapies, PBMT and TENS, are commonly used in clinical practice for patients with neck pain. The use of these electrophysical agents is important to decrease pain and may have the added benefits of decreasing the use of painkillers and facilitating exercise during therapy. However, the literature is still controversial, the studies are heterogeneous and of low quality and most of them only investigated pain and functional impairment. Therefore, more high-quality trials are required to verify the efficacy of these agents and the best methods of applying them. In addition, until this moment, no studies were found that investigated the combined effect of PMBT and TENS. These electrophysical agents have different ways of producing analgesia so we hypothesize that combined treatment with PMBT and TENS may have a synergistic action and result in a decrease in pain faster and/or for a longer time. Therefore, the objective of this study is to verify the efficacy of PBMT and TENS, isolated or combined, in relation to pain, functional disability, range of motion, pressure pain threshold, temporal summation, conditioned pain modulation, depressive symptoms, pain catastrophizing, quality of life, analgesic intake, and global perceived effect in patients with non-specific chronic neck pain.

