### Inclusion criteria

2.4

Patients with non-specific chronic neck pain, defined as pain or discomfort in the posterior cervical region between the superior nuchal line and the first thoracic spinous process and/or shoulder girdle;Neck pain for at least 3 months;Neck disability index (NDI) score of 5 points or higher;Numeric rating scale (NRS) score of ≥3 for pain intensity;Aged between 18 and 65 years;Men and women.

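### The global perceived effect question printed in section 2.19 asks neck-pain patients about their back

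*Protocol article*

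**What the plan says.** Section 2.19 (Global perceived effect) describes an 11-point scale from –5 to 5 on which higher is better. It introduces the instrument as follows: "The global perceived effect (GPE) scale, translated and validated for Portuguese". It then gives the timing, "At baseline, after the treatment, and at follow-up, the patients will be asked", and the question itself: "Compared to when this episode first started, how would you describe your back these days".

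The rest of the article is about the neck. The objective at the end of the Introduction lists "global perceived effect in patients with non-specific chronic neck pain" among the outcomes. The first inclusion criterion (section 2.4) reads "Patients with non-specific chronic neck pain, defined as pain or discomfort in the posterior cervical region between the superior nuchal line", extended there to the shoulder girdle. Section 2.8.2 lists GPE as a secondary outcome and adds: "Pain intensity and global perceived effect will also be measured in contact by telephone after 6 weeks randomization".

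**The concern.** The question names a body region that is neither the condition under study nor an entry criterion. A patient without back symptoms has no natural answer to it. A patient with unrelated back symptoms could answer sincerely about something that the trial did not set out to treat. Others would take it to mean their neck. The resulting scores would mix answers about different regions, and the recorded score alone would not show which region a patient had in mind.

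At stake is one secondary outcome. It carries more weight at 6 weeks than at the end of treatment, because only pain intensity and GPE are collected at that contact. The contact is by telephone, so the spoken wording is all that the patient has to go on.

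**Working it through.** No figure in the plan depends on this item, so there is none to reproduce. The sample size (section 2.22) rests on the pain numerical rating scale. The check is a comparison of the printed item with the rest of the article.

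1. **Region named in the item.** Section 2.19: the back. The neck is not mentioned in the question.
2. **Region that defines the population.** Section 2.4: posterior cervical region and/or shoulder girdle. Back pain is not an inclusion criterion.
3. **Region in the objective.** Introduction: GPE is named as an outcome in patients with neck pain.
4. **Wording of another patient-reported item.** Section 2.18 asks patients to record medication used for their neck pain. The article names the neck there, so generic wording is not its consistent practice.
5. **Any statement that the region is adapted.** None. Section 2.19 describes a Portuguese translation and validation, but no neck version.
6. **Other places where the back could come in.** The Introduction's definition of chronic neck pain allows pain "with or without pain referred to the upper back or arms and continuing for at least 3 months". The pressure pain threshold sites in section 2.12 include points beside T4 and T8. Referral is optional and appears only in the background definition, and the thoracic points are test sites. Neither makes the back the target region.

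Items 1 to 3 contradict each other, and items 4 to 6 do not resolve the contradiction.

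**Direction of the consequence.** Let q be the share of patients who answer about the back, D_neck the true group difference in a neck-directed GPE score, and D_back the difference in a back-directed score. If q is the same in every arm, and those who answer about the back are otherwise like the rest, the expected observed difference is

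(1 − q) × D_neck + q × D_back.

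Whenever D_back is smaller than D_neck in the same direction, or nil, this lies closer to zero than D_neck. The result is dilution. Mixing two kinds of answer also adds spread wherever the average back rating and the average neck rating differ.

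**Size of the consequence.** The document gives no value for q, D_neck or D_back, and no variance for GPE. The loss therefore cannot be calculated from it.

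**The case against.** Four points can be made in the plan's defence.

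- **The printed sentence may not be the working script.** The trial runs in São Carlos with a Portuguese instrument, and the article is in English. The sentence may be generic instrument wording while the form names the neck. This stands as a limit on what can be claimed about harm. It does not clear the text, because the article presents the sentence in quotation marks as what patients will be asked.
- **The opening of the question anchors the answer.** It refers to the current episode and is put to people recruited and treated for neck pain, by an evaluator who also collects their neck outcomes. Many would understand what was meant. This stands in part: it makes a wholesale misreading unlikely, but it does not make the wording right.
- **The back is not wholly separate from the complaint.** Pain may be referred to the upper back, and treatment is applied to the painful area as the patient reports it. For some patients the two regions may overlap. This stands for those patients only.
- **The stakes are limited.** GPE is one of eleven secondary outcomes in section 2.8.2. The primary outcome is pain intensity after 10 sessions, and pain intensity is also collected at 6 weeks. This stands in full.

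A reader might go further and infer that GPE would be uninterpretable, or that a definite part of its effect would be lost. The document supports neither. The first needs patients to take the question literally and to have back ratings unrelated to their neck complaint. The second only returns its own assumption: with D_back set to nil, an assumed q of 25–75% gives a loss of 25–75%, and no figure from the trial enters the sum.

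**Conclusion.** Section 2.19 is wrong as written: it prints an outcome question about the back in a trial whose population and objective concern the neck. This is an error in stated text, not a detail that an article would leave to a fuller document. Severity is moderate. If the item is asked as printed, some patients may rate the wrong region, which adds noise to GPE and probably pulls the group difference towards zero, both after treatment and at 6 weeks. The expectation of dilution assumes that misreading is about equally common in each arm and that any treatment difference in back ratings is smaller than in neck ratings. The amount cannot be derived from the document.

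Confidence is high for the printed text and lower for the harm, because the Portuguese form and the telephone script are not shown. It should not be inferred that patients have been, or will be, asked about their backs. The primary comparison, the randomisation and the sample size are unaffected.

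**What to change.** - In section 2.19, change the region in the question from the back to the neck.
- Check the Portuguese data-collection form and the telephone script for the 6-week contact. Correct them if they also say back, ideally before the first patient is assessed. If they already name the neck, only the article's text needs correcting.
- If any patients were already asked the back version, flag those records by assessment time and report GPE with and without them.

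The cost is one word in the protocol and, if needed, in the form and script, plus one extra GPE analysis if any records are flagged. No stated figure in the plan changes.
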